#### Withdrawal of study participants

Participants may provide consent but later choose to withdraw from the study. The frequency and timing of the withdrawal will be recorded. If a participant chooses to withdraw from the study and not participate in further follow-ups, the data collected up to the point of withdrawal will still be retained.

#### Equality Health-CVD intervention

The intervention is delivered primarily through home visits, with alternative options for telephone or video call to ensure flexibility based on individual needs. Each session is tailored towards the specific needs of the participant, including a coaching session on what matters to them and goal setting. Health checks are conducted on week 1 and 12 to elicit a health-related conversation, and participants are provided with support linked to social connection and wider determinants of health. The Equality Health Advisor may assist participants in navigating different services which may include contacting service providers on their behalf.

The intervention comprises 4 sessions spaced approximately 4 weeks apart. Between sessions participants work on their identified goals and engage with public or community services. The follow-up sessions will provide additional support, monitor progress, and address any emerging needs and barriers. Should barriers arise, the participant and the Equality Health Advisor will collaborate to identify solutions. Information about delivery time, mode, application of intervention components, and retention/adherence rate will all be gathered by the Equality Health Advisor using the equality health home visit form. These records will later be transferred to an excel sheet. At the end of each session the Equality Health Advisors complete a reflective log.

At the final session (week 12) participants will reflect and discuss their achievements, any potential setbacks encountered, and strategies to maintain or build upon their achievements and progress. The participant will also undertake a second health check and complete Case Report Form B with the Equality Health Advisor.

As part of the final intervention process evaluation, a subset of participants (approximately 10–15) will be selected randomly using a non-probability convenience sample [44] and will participate in a semi-structured interview during the 12-week follow-up visit. The semi-structured interviews will be conducted by the lead researcher and will either be conducted face to face in the participants’ home using an audio device or via video link.

The interviews will explore the following themes:Participant’s experiences and perceptions of the Equality Health-CVD InterventionAcceptability of the intervention and study design.Challenges or opportunities of future research in reducing health inequalities in the community.

In addition, the Equality Health Advisors will also participate in semi-structured interviews to explore their views of the Equality Health-CVD study using a similar thematic qualitative approach.

During the development of the protocol, the lead researcher conducted a public and community asset mapping exercise to identify services, activities, and local contacts available across the five local authorities in Gwent. All information was added to templates with the aim to help the Equality Health Advisors to navigate public and community asset provision.

A series of patient and professional consultations were organised to inform the co-design of the protocol and intervention. To support the intervention, health check equipment was purchased, and an Equality Health Adviser Handbook was created. This handbook aims to provide a framework for delivering the Equality Health-CVD intervention focusing on four dimensions of the adapted Labonte model (Table 4).

**Table 4 Tab4:** Intervention procedures

Procedure	Timepoints (Weeks)
Eligibility criteria review	Week 0
Informed consent	Week 0
Medical history	Week 0
Case Report Form A (incl. AUDIT-C)	Week 0
Health Check (Weight, HR, BP, BMI, Waist Circumference)	Weeks 1 and 12
EQ-5D	Weeks 0 and 12
PROMIS-10	Weeks 0 and 12
South Wales Social Wellbeing Scale	Weeks 0 and 12
Equality Health Home Visit	Weeks 1, 4, 8, 12
Case Report Form B (incl. AUDIT-C)	Week 12
Semi-structured interview	Week 12

The Equality Health Advisors are employed by the Aneurin Bevan University Health Board within the Public Health Team. Prior to study implementation, the Equality Health Advisors received additional training to support safe and effective communication with participants, which included a health coaching course, first aid emergency responder, and various online courses in clinical skills, service navigation, and community engagement.

To balance protocol fidelity with real-world feasibility, consultations may be scheduled within a ±14-day window around target dates.Consultation 2: target week 4 (deliverable weeks 2–6)Consultation 3: target week 8 (deliverable weeks 6–10)Consultation 4: target week 12 (deliverable weeks 10–14)

This flexibility reduces unnecessary barriers to participation, including work schedules, caregiving responsibilities, health fluctuations, or any additional challenges that may arise (Table 4).

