*SPIRIT*: overview of Equality Health-CVD. Subscript digit one (1) indicates the following: At baseline, socio-demographic information will be collected, including age, gender, ethnicity, living arrangements, pain level, smoking status and Audit C, Alcohol Use Disorders Identification Test.; superscript two (2) indicates the following: physical testing assessments to identify health risk factors and health status; subscript digit three (3) indicates European Quality of Life 5 Dimension Level 5; subscript digit four (4) indicates the following: PROMIS-10, Patient-Reported Outcomes Measurement Information System Global Health; subscript digit five (5) indicates the following: The South Wales Social Wellbeing Scale (SWSWBS); subscript t digit six (6) indicates the following: End of intervention evaluation items and Audit C, Alcohol Use Disorders Identification Test; subscript digit seven (7) indicates the following: participants semi structured interview questions that will be completed at the final follow up visit; subscript digit eight (8) indicates the following: Equality Health Advisor semi structured interview questions that will be completed at the end of the study

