### Study design

This feasibility study is a UK-based single-site pilot study of the Equality Health–CVD intervention. The intervention consists of four home visits encompassing health checks, coaching, support linked to social connections and wider determinants of health delivered by Equality Health Advisors over a 12-week period. Tables 2 and 3 logic model articulates the conceptual framework of the Equality Health–CVD intervention including how the context, intervention activities interlink with perceived impact and outcomes.

**Table 2 Tab2:** Equality Health-CVD logic model

Context	Intervention	Mechanisms of impact	Intervention outcomes

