#### Participants

The study aims to recruit 20 participants between October 2024 and August 2025. Participants in the study will undergo eligibility screening in various hospital sites across the Aneurin Bevan University Health Board. Recruitment will be achieved by approaching all appropriate outpatient clinics. Eligible participants will be provided with verbal information about the study and given a copy of a patient information sheet by the Aneurin Bevan University Research Team. Participants will be given adequate time to review the information sheet and ask questions. Participants may choose to give consent on the same day or take the information home to consider. In this case, patients will have the option to be contacted by the research team or given the contact details of the research team to arrange a follow-up appointment. Consented participants will self-complete Case Report Form A, which includes demographic and SDoH profile data collection (housing, income, social support, service access barriers) and various validated social and wellbeing patient-reported outcome measures. Thereafter, participants will be offered the first Equality Health appointment at a convenient time for the participant.

Potentially eligible participants will reside in Gwent, where identification, screening, and consent will take place at various sites across Aneurin Bevan University Health Board in Wales during a routine outpatient appointment or as an inpatient.

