### Outcomes

#### Primary

The primary outcome is to evaluate the feasibility and acceptability of the Equality Health–CVD study in terms of recruitment and retention rate to the intervention (Study objective 1). A record will be kept of the number of participants recruited within 9 months of the study opening, including the number of participants who participated in the 12-week follow-up. Additionally, a feasibility assessment of intervention fidelity will be conducted (Study objective 2). This will involve documenting the number of home visits completed, recording the data collected during each visit, and tracking the outcomes of signposting to community and public assets.

Secondary outcomes: the secondary outcomes will examine the experiences and acceptability of the intervention from the perspectives of both participants and deliverers (Equality Health Advisors). This evaluation linked to (objective 3 and 4) will include identifying barriers and facilitators to delivery as well as perceived impacts. Data will be collected through qualitative semi-structured interviews conducted at the end of the intervention for participants and at the end of the study for Equality Health Advisors. To complement these findings, reflective diaries maintained by Equality Health Advisors during home visits will also be analysed.

In addition, participants will complete a series of validated questionnaires at baseline and 12 weeks post-baseline as part of the feasibility study's evaluation. These quantitative Patient-Reported Outcome Measures (PROMs) will be used in conjunction with qualitative semi-structured interviews as data descriptors. This will facilitate whether the participants are willing and able to complete these measures, in addition to capturing subjective health and social wellbeing outcomes that may enhance data richness.

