## Research methods

### Quantitative data

The following questionnaires will be completed at baseline and post-baseline week 12.Case Report Form A will collect demographic data including wider determinants of health.PROMIS 10—the PROMIS 10 is a comprehensive and accessible set of tools used to measure self-reported physical, mental, and social health, including symptoms, function, and general perceptions of health and wellbeing [45].South Wales Social Wellbeing Scale—The South Wales Social Wellbeing Scale (SWSWBS) is a tool to the quality of respondents’ overall experience of social wellbeing via the external social resources they possess, their perceived ability to engage in and enjoy the social world in which they live, and, as a result, their capacity for human functioning and flourishing [46].EuroQol-5D—EQ-5D is an instrument which evaluates the generic quality of life developed in Europe and widely used. The EQ-5D descriptive system is a preference-based HRQL measure with one question for each of the five dimensions that include mobility, self-care, usual activities, pain/discomfort, and anxiety/depression [47].Case Report Form B will collect data satisfaction of feasibility and implementation.

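### Questionnaires are self-completed at baseline but Case Report Form B is completed with the deliverer at week 12, which risks favourable answers and leaves unaided week-12 completion unassessed

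*Protocol article*

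**What the plan says.** **Baseline.** The Participants section states: "Consented participants will self-complete Case Report Form A, which includes demographic and SDoH profile data collection". The same sentence adds "various validated social and wellbeing patient-reported outcome measures". The first advisor appointment is offered only afterwards.

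**Week 12.** The section on the Equality Health-CVD intervention says of the final session: "The participant will also undertake a second health check and complete Case Report Form B with the Equality Health Advisor". In that session participants also look back on what they achieved.

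**Who the advisor is.** The Study design section describes "support linked to social connections and wider determinants of health delivered by Equality Health Advisors over a 12-week period". The person beside the participant at week 12 is a deliverer.

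**What CRF B holds.** The Quantitative data section says: "Case Report Form B will collect data satisfaction of feasibility and implementation". The footnote to Table 1 describes the form as "End of intervention evaluation items and Audit C, Alcohol Use Disorders Identification Test". The Data management and monitoring section names CRF A and CRF B together as the source of the PROMs.

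**What the PROMs are for.** Under Outcomes, the protocol says of collecting them: "This will facilitate whether the participants are willing and able to complete these measures". It also gives them a descriptive role alongside the interviews.

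**The concern.** Three things are at stake.

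1. **Satisfaction.** Participants answer questions about the service in the company of the person who provided it. The logic model counts a trusting relationship with the advisor among its mechanisms, so courteous answers are plausible.
2. **Change.** Baseline forms are self-completed and week-12 forms are completed with the deliverer. Mode of completion and the deliverer's presence are thus fully confounded with time. There is no control arm, and the mode does not vary within a time point, so no analysis can separate them. AUDIT-C asks about alcohol and is especially open to socially desirable answers.
3. **Feasibility of data collection.** RQ2 asks whether data collection is feasible, and the PROMs are meant to show whether participants will and can complete them. A form completed with the advisor does not show that at week 12.

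**Working it through.** The documents give no standard deviation, expected change or size of mode effect, so there is no figure to reproduce. The check sets the relevant sections side by side.

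| Item | Baseline | Week 12 | Mode differs? |
|---|---|---|---|
| PROMs (EQ-5D, PROMIS-10, social wellbeing scale) | Part of CRF A, self-completed (Participants) | Apparently in CRF B (Data management and monitoring), completed with the advisor | Yes, if they are in CRF B |
| AUDIT-C | In CRF A, self-completed (Table 1 footnote; Participants) | In CRF B, completed with the advisor | Yes |
| Satisfaction and evaluation items | Not collected | In CRF B, completed with the advisor | No baseline; answered with the deliverer |
| Health check | Done by the advisor | Done by the advisor | No |

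**Step 1: is the difference stated or inferred?** For AUDIT-C and the satisfaction items it follows directly from the text. For the three PROMs it rests on the data management section. Tables 1 and 4 list the PROMs on rows separate from CRF B. Those tables separate the PROMs from CRF A in the same way, although the Participants section says CRF A includes them. Separate rows therefore do not show that the PROMs lie outside CRF B. The inference is plausible, but no section says outright that each PROM is completed with the advisor.

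**Step 2: what does completing a form *with* the advisor mean?** The text does not say whether the advisor reads the items aloud, records the answers or is only present. The data management section has advisors populate the home-visit data (Level 2) and places CRF A and B data in Level 1. It does not show that advisors write down CRF B answers. Under any of these readings the deliverer is involved.

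**Step 3: does it reach the progression criteria?** The acceptability criterion lists reflective diaries and 12-week interviews as its data, not CRF B, and has no threshold. The lead researcher conducts the participant interviews. The recruitment and retention thresholds do not depend on what participants answer. The effect is therefore confined to the CRF B satisfaction items, the descriptive change in AUDIT-C and (apparently) the PROMs, and the evidence on completion at week 12.

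**Step 4: what still informs ability to complete?** Self-completion of CRF A tests it at baseline. Only unaided completion at week 12 is left open.

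**Step 5: does the route of return matter?** Retention is read from the 12-week questionnaire, among those who complete at least one session. With at most 20 in that denominator, each unreturned form lowers measured retention by at least 100/20 = 5 percentage points. The amber band, 50–65%, is only 65 − 50 = 15 points wide, so three lost forms (3 × 5 = 15) span it. A remedy relying on postal return could disturb a progression criterion.

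**The case against.** The strongest reply is that little depends on these data. The PROMs are descriptors, the Study limitations section rules out conclusions on effectiveness, and no test or effect estimate is stated. Participant acceptability is explored in interviews by someone other than the deliverer. The article is also a condensed text, so details of administration may sit in the advisor handbook or the data management plan.

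Much of this stands, and it limits the weight of the point. A reader might infer that the acceptability finding itself is biased. The documents do not support that, because CRF B is not among the sources of that criterion; at most there is an indirect influence, since the interview is held at the same visit. A reader might also infer that satisfaction scores are inflated as a matter of fact, or by some fraction of a standard deviation. The documents support neither: the direction is plausible, but the size would rest wholly on assumed figures. Nor is it right that the design conceals whether participants can complete the measures, since baseline still tests that.

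The reply does not remove the core. The article states both modes and they differ, so this is not a detail left out. Outcomes will be reported descriptively by condition, and the Discussion expects the data to inform the design of a later trial. The question of unaided completion belongs to feasibility and is untouched by the disclaimer on effectiveness.

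**Conclusion.** The point holds in a limited form. Mode of completion and deliverer involvement change together between baseline and week 12. This is certain for AUDIT-C. For the PROMs it depends on reading the data management section as placing them in CRF B. The satisfaction items, collected only at week 12, are answered with the deliverer. Favourable answers are a credible risk of unknown size. Unaided completion at week 12 cannot be assessed as written, so part of a stated purpose goes unmet. No traffic-light threshold, sample-size figure or formal acceptability criterion is directly affected. This is a cheap improvement and not a flaw that threatens the study's main conclusions.

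**What to change.** In the section on the Equality Health-CVD intervention, state that CRF B and the week-12 PROMs are self-completed, as at baseline. Participants should do so during the week-12 visit but out of the advisor's sight, then seal the forms and hand them over before the visit ends. Handing over at the visit, not posting, keeps the retention measure unaffected. State explicitly that the PROMs belong to the week-12 pack, so that the tables and the data management section agree.

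Record any assistance given and by whom. Under RQ2, report the proportion completing unaided and the item missingness at both time points.

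The cost is some envelopes, a line in the advisor handbook and an assistance field on the form. The downside is possibly a few more missing items, which is a feasibility result the study wants to know. If forms already collected were completed with the advisor, report that mode next to the week-12 results and draw no conclusion from them about unaided completion.

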#### Study population: inclusion and exclusion criteria

This feasibility study deliberately includes patients with three related vascular conditions: a history of ischaemic stroke, National Institutes of Health Stroke Scale (NIHSS) score of less than 5, a history of transient ischaemic attack (TIA), or a referral to a Peripheral Vascular Clinic. This heterogeneous approach is justified on theoretical and pragmatic grounds. All three conditions result from atherosclerotic vascular disease sharing common mechanisms and modifiable risk factors [9–12]. Additionally, the Equality Health-CVD intervention targets the person and their environment, not the specific vascular pathology. Heterogeneity will be mitigated through baseline characteristics reported by condition subgroup, recruitment/retention rates analysed by pathway and qualitative interviews will be examined for any emerging diagnosis-specific themes that may inform future trial design.

Participants eligible for recruitment in this study are those aged 18 years or older. Eligible participants must also have the capacity to provide informed consent and express a willingness to participate in a qualitative interview at the conclusion of the intervention. Exclusion criteria include patients receiving or eligible for palliative care. Unwillingness or inability (e.g. physical or cognitive) to comply with study procedures. Patients already participating in a clinical rehabilitation home intervention and with an unwillingness to take part in a qualitative interview at the end of the intervention are also excluded.

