#### Sample size

The sample size of 20 participants is appropriate for a feasibility study and aligns with published guidance on feasibility trial design [41–43]. The participants will be selected through convenience sampling; this decision was made due to time and resource constraints [44]. The study will remain open for 12 months. Recruitment progress will be closely monitored, and strategies will be adapted as needed to ensure target enrolment is achieved. The study will remain open until October 2025, at which point it will close for data analysis.

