**Table Taba:** 

Linked RQ	Progression criteria		Green light	Amber light	Red light	Data
	N	Detail				
1. Recruitment	1	% of target number of participants recruited (target: 20; 9 -month recruitment period)	>75%	60–75%	< 60%	*Screening log* *Baseline, RN – Informed Consent Form CRF A*
1. Retention	2	% of patients who participate in 12-week follow-up (of those who complete min. 1 intervention session)	>65%	50–65%	<50%	12-week follow up questionnaire
2. Feasibility of intervention implementation	3	The intervention is implemented with fidelity (i.e., 4 home visits conducted with data collected recorded at each visit and signposting to community and public assets)	No traffic light criteria to be applied			HEA reflective diaries 12-week interview data
3. Acceptability of the intervention	4	Data indicates the intervention is acceptable to participants and deliverers				HEA reflective diaries 12 week interview data

The Green light system (progression criteria) indicators are as follows:Green—indicates current procedure can be used for future studyAmber—indicates current procedure needs attention with discussion for optimisation in future studyRed—indicates current procedure is unacceptable and not feasible therefore an alternative will need to be tested within a future study

The Study Management Group (SMG), which includes an ABUHB Quality Assurance Officer, an Independent Data Validation Reviewer (Quantitative), and an Independent Data Validation Reviewer (Qualitative), will review all aspects of the progression criteria.

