### Qualitative data collection

#### Participant interviews

Semi-structured interviews will be conducted using a sub-sample of participants (*n* = 10–15) and will examine intervention acceptability using the Theoretical Framework of Acceptability [48]. The TFA provides a systematic approach to understanding intervention engagement using seven constructs. Interview questions aim to allow participants to describe experiences naturally. TFA coding will be applied retrospectively during analysis, an approach endorsed by Sekhon et al. [48].

In addition to acceptability assessment, participants' interviews will examine whether the intervention operated according to its theoretical framework, (the adapted Labonte Model) (RQ2). The analysis will assess which dimensions participants experienced most strongly, whether all four were activated in practice, and how dimensions interacted.

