#### Equality health advisor interviews

Semi-structured interviews with Equality Health Advisors will examine implementation feasibility from deliverers’ perspectives, using inductive thematic analysis [49, 50]. In addition, Equality Health Advisor reflection diaries will be analysed to confirm intervention delivery intention, including challenges, successes, and suggestions for improvement.

Interviews will be conducted in person, though a video/telephone call option will also be available. Interviews will be audio recorded and transcribed, and information will remain confidential. Analysis will employ a combined deductive-inductive approach:Deductive Frameworks: TFA seven constructs and Labonte four dimensions (participant interviews)Inductive themes: emergent theme beyond frameworks (participant interviews) and implementation insights from Equality Health Advisor data.

Coding will involve systematic assignment of data segments to framework constructs and/or emergent themes, with patterns identified across participants. Reporting will follow the guidelines set by the Consolidated Criteria for Reporting Qualitative Research (COREQ) [51]. Member checks will also be conducted to ensure credibility and confirmability. Data collection will continue until saturation is reached. If new data continue to emerge after the final interview, additional interviews may be conducted. Triangulation across quantitative feasibility metrics, participant TFA findings and Equality Health Advisor implementation insights aims to provide a thorough summary of intervention acceptability and deliverability, informing progression decisions and refinement recommendations.

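### Interviewees are described as both randomly and conveniently sampled, and participants' own accounts of acceptability can come only from people who attend the week-12 visit

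*Protocol article*

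**What the plan says.** All references are to the protocol article.

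- **Selection and timing.** The section on the Equality Health-CVD intervention says that a subset of about 10–15 participants "will be selected randomly using a non-probability convenience sample [44] and will participate in a semi-structured interview during the 12-week follow-up visit". The interview is face to face at home or by video link.
- **Purpose.** Under Participant interviews: "Semi-structured interviews will be conducted using a sub-sample of participants (*n* = 10–15) and will examine intervention acceptability using the Theoretical Framework of Acceptability".
- **Timing elsewhere.** The Outcomes section says "Data will be collected through qualitative semi-structured interviews conducted at the end of the intervention for participants and at the end of the study" for the advisors. Table 1 puts the participant interview at T4, and Table 4 puts it at week 12.
- **Entry condition.** Participants must "express a willingness to participate in a qualitative interview at the conclusion of the intervention". The exclusion list repeats the condition: those "with an unwillingness to take part in a qualitative interview at the end of the intervention are also excluded".
- **Other participant source.** Case Report Form B, on satisfaction with feasibility and implementation, is completed at week 12 with the Equality Health Advisor.
- **Early stopping.** The withdrawal section records how often and when people withdraw, and keeps their data to that point. It mentions neither an exit contact nor reasons.
- **Use.** Criterion 4 (acceptability to participants and deliverers) draws on advisor diaries and 12-week interview data and has no traffic-light threshold.
- **Further interviews.** "Data collection will continue until saturation is reached", with extra interviews possible if new data still emerge.

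**The concern.** There are two problems of different weight.

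The first is a contradiction. A random sample gives every member of a listed frame a known chance of selection. A convenience sample takes whoever is easiest to reach. The sentence claims both, so the interviewer cannot tell which to do, and a COREQ report, which the article promises, could not describe the sampling truthfully.

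The second is selection. RQ3 asks whether the intervention is acceptable to participants. People who find it burdensome or unhelpful are, plausibly, more likely to stop or to miss the last visit, and that is the point at which participants are asked. The article says its findings will determine whether the intervention is feasible and acceptable enough to justify an effectiveness trial. A one-sided account of acceptability would feed that decision and would leave the next trial short of first-hand information from those who left. The Study limitations section discusses selection at recruitment but not this selection at interview.

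**Working it through.** The article gives no formula for the 10–15 interviews, and it supports the total by reference to guidance ("The sample size of 20 participants is appropriate for a feasibility study and aligns with published guidance on feasibility trial design"), so there is no figure to reproduce. The check is a count at the article's own cut-offs.

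**Inputs (Progression criteria table).** Recruitment target 20: green above 75%, amber 60–75%. Retention: green above 65%, amber 50–65%, where retention is the percentage "of patients who participate in 12-week follow-up (of those who complete min. 1 intervention session". Planned interviews: 10–15.

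**Assumption.** Everyone recruited has at least one session, so recruits and the retention denominator coincide.

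**Step 1. Recruitment ranges.** Green: more than 0.75 × 20 = 15, so 16 to 20. Amber: 0.60 × 20 = 12 to 0.75 × 20 = 15.

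**Step 2. Outside the interview frame when both criteria are green.** For N starters, the smallest green attendance is the smallest whole k with k/N > 0.65. The number outside the frame is N − k.

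| N | smallest k | k/N | outside frame |
|---|---|---|---|
| 16 | 11 | 68.8% | 5 (31%) |
| 17 | 12 | 70.6% | 5 (29%) |
| 18 | 12 | 66.7% | 6 (33%) |
| 19 | 13 | 68.4% | 6 (32%) |
| 20 | 14 | 70.0% | 6 (30%) |

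**Step 3. Attenders when both criteria are amber.** k must satisfy 0.50 ≤ k/N ≤ 0.65.

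| N | possible k |
|---|---|
| 12 | 6–7 |
| 13 | 7–8 |
| 14 | 7–9 |
| 15 | 8–9 |

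Ten attenders would give 10/14 = 71.4% or 10/15 = 66.7%, both already green. The maximum is therefore 9, one short of the lower interview target. At both lower limits, 6 of 12 (50%) are outside the frame.

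**Step 4. When only one criterion is amber.** With 20 starters, amber retention gives 10 to 13 attenders, so 10 interviews are possible. With 16 starters, the lower amber limit gives 8, so they are not. With 15 starters, the lowest green retention gives 10. With 12 starters it gives 8. A shortfall is then possible but not certain.

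**Step 5. Possible size of the bias, on assumed rates that are not in the article.** Let r be retention, and let a1 and a0 be the proportions of attenders and non-attenders who find the intervention acceptable. Overall acceptability is r × a1 + (1 − r) × a0, while interviews of attenders show a1. With r = 0.70:

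- a1 = 0.90, a0 = 0.30: 0.63 + 0.09 = 72%, against 90% seen.
- a1 = 0.90, a0 = 0: 0.63 + 0 = 63%, against 90% seen.
- a1 = 0.80, a0 = 0.50: 0.56 + 0.15 = 71%, against 80% seen.

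If a0 equals a1 there is no bias. The article gives no basis for choosing among these cases.

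**The case against.** The defence has real substance, and it rules out several stronger readings that a reader might infer.

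- *That only those who finished the intervention judge its acceptability.* The documents do not support this. Criterion 4 also uses advisor diaries, written at every visit and so covering people who later leave. Advisor interviews are added, all sources are triangulated with the feasibility counts, and the Outcomes section treats recruitment and retention themselves as measures of acceptability. Attending week 12 also does not require all four visits.
- *That people who found it unacceptable are never heard.* Attenders may be critical, and early stoppers may leave for unrelated reasons. The entry condition acts before anyone has experienced the intervention.
- *That criterion 4 is bound to be met.* It has no threshold to pass, heavy drop-out would show in criterion 2, and the group reviewing the criteria includes an independent qualitative reviewer.
- *That any amber result makes the interview target or saturation unreachable.* Step 4 shows otherwise for the target, which is itself approximate. Saturation is not a count.
- *That reasons for stopping are not collected at all.* The article is a condensed account, and the contents of the forms and diaries are not shown.

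The percentages in Step 2 are also extremes at the cut-offs, not expected values.

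What remains is that diaries and advisor interviews are the deliverers' view. They cannot replace participants' own accounts, which is what RQ3 asks for. Every stated timing for those accounts is week 12.

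**Conclusion.** The point holds in this form. The sampling sentence contradicts itself. First-hand participant evidence on acceptability is conditioned on attending week 12 and on having agreed at entry to be interviewed. The likely direction of bias is towards acceptability. Its size cannot be derived from the article and depends on how far early stoppers differ from attenders.

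If every recruit starts, about three in ten could be outside the interview frame with green results (5 of 16 or 6 of 20, and at most 6 of 18). The minimum of 10 interviews is certain to be missed only when recruitment and retention are both amber. The recruitment and retention counts are unaffected, except that the entry condition could itself lower recruitment. This should be corrected because acceptability feeds the decision to proceed, but it does not undermine the study as a whole.

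**What to change.** 1. Replace the sampling sentence with one named method: purposive sampling from all participants who had at least one session, by attendance (week-12 attender or early stopper) and by diagnosis. This also serves the diagnosis-specific themes that the article promises.
2. Keep the total at 10–15. Within it, invite willing early stoppers to a voluntary interview when they stop.
3. State the interview mode. For participants, the intervention section gives only face to face or video; the telephone option stands under the heading for advisor interviews.
4. Record any reason for stopping that the participant volunteers, and describe early stoppers' views alongside attenders' when reporting criterion 4.
5. Add to Study limitations that willingness to be interviewed was a condition of entry.

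**Cost.** The number of interviews does not grow. A minor ethics amendment may be needed, because agreement at entry covers an interview at the conclusion of the intervention, and some early stoppers will decline. If recruitment has closed (the article plans it to end in August 2025 and the study to close in October 2025), correct the sentence to say what was done, compare the baseline characteristics of interviewees with those of non-attenders, and add the limitation.
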